**Figure 1 F1:**
[figure not shown]
Flow of the study.

### Study design

This is a multicentre, randomised, triple-blind placebo-controlled, cross-over study in patients with hypertension and a history of cardiovascular events under treatment with low-dose ASA taken during the day time.

Patients will be randomly selected from the target population of each primary health practitioner that collaborates in the study. This first randomization will be performed by the Primary Care Research Unit of Bizkaia (PCRUB). After that, they will be randomly and blindly assigned to two successive sequences of bedtime and daytime administration of ASA, the drug and placebo both being manufactured by Laboratorium Sanitatis. One group of patients will take ASA over a period of 2 months at bedtime and placebo in the mornings, while in the second period they will take ASA in the mornings and placebo at bedtime (BD sequence). The other group will follow the opposite sequence (DB sequence).

On inclusion in the study, all participants will be prescribed the same standard dose of 100 mg ASA/day. Between the two periods there will be a washout period of 15 to 30 days (selecting the most convenient time for each patient, as explained below), during which all patients will take ASA in the mornings. Despite the fact that the half-life of ASA ranges from 2 to 20 h, its potential hypotensive effect may be mediated by mechanisms associated with the physiology of vascular epithelium that may last for much longer (as much as a week), regardless of whether the ASA itself has been cleared from the body. In the light of current knowledge, a washout period of at least 15 days should be sufficient for the effect of the first sequence of treatment not to interfere with that of the second period. The results will be assessed by monitoring BP at baseline and 2, 3 and 5 months after the intervention.

### Setting

The study is intended to be conducted in a total of 20 primary care centres: six in Bizkaia and six in Gipuzkoa, all managed by the Basque Health Service-Osakidetza, and a further eight in Barcelona, managed by Catalan Health Service. In addition, each of the health centres are linked to the PCRUB or the Jordi Gol Foundation (in the Basque Country and Catalonia respectively), as well being members of the Primary Care Research Network (redIAPP) for research into preventative activities health promotion, and of the Consortium to Support Biomedical Research Networks (CAIBER).

The primary health centres in the Barcelona region are: Santa Coloma de Gramanet, el Maresme, Badia del Valles, Gotic, Passeig de Sant Joan, Sant Martí de Provençals, Passeig Maragall and la Mina; the centres in Bizkaia are: el Karmelo, Gasteleku, Areilza, Solokoetxe, Basurto and Kueto; and, finally, those in Gipuzkoa are: Andoain, Oñati, Zumárraga, Tolosa, Ermua and Azpeitia. The doctors and nurses collaborating in the study are all primary care health professionals, and the patients who will participate are those they regularly see in appointments at the health centres.

The health centres have offices for medical and nursing appointments, blood collection facilities and rooms for performing other types of tests, as well as all the other equipment necessary for undertaking this study. Nevertheless, in order not to disrupt the normal operation of the centres in relation to ABPM, all will be provided with the equipment required for performing the BP monitoring necessary for this study.

The PCRUB will be in charge of the coordination of the performance and monitoring of the fieldwork, as well as the quality assurance and control and the statistical analysis of data collected for the study. For this purpose, it has:

•Meeting rooms with informatic support to hold coordination meetings and training sessions for collaborating researchers

•A centralised database, with various levels of access for users from each of the participating health centres, specifically designed for this study

•Licences for software for statistical analysis (SAS)

•Support staff to perform technical and administrative tasks, coordination, monitoring, and quality assurance and control, as well as the statistical analysis of data

### Participants

#### Inclusion criteria

To be eligible for inclusion patients will need to:

•Be aged >18 years of either sex

•Have diagnosis of hypertension

•Have treated hypertension; this is when at least the patient receives one antihypertensive drug

•Be primary care users in which anti-hypertensive drug regimen has not been changed in the last 3 months

•Have a medical history of a cardiovascular event at least 6 months previously (ischaemic heart disease, cerebrovascular accident (CVA), peripheral arterial disease) and have been treated at least for 3 months with low doses of ASA (75–125 mg)

•Sign an informed consent form

•Complete, prior to inclusion, a washout period of 1 month during which they take ASA in the morning, if they had been under regular treatment with ASA at bedtime

#### Exclusion criteria

Patients will be excluded if they meet any of the following criteria:

•Being pregnant or breastfeeding

•Having poorly-controlled high blood pressure, defined as having a systolic BP >150 mmHg or a diastolic BP >95 mmHg in two successive health checks

•Requiring non-steroidal anti-inflammatory drugs (NSAIDs) on a daily basis

•Having a severe or terminal disease

•Being diagnosed with a physical or mental disorder that would hinder their collaboration

•Taking other antiplatelet or anticoagulant agents concomitantly

•Being on ASA at doses outside those stated in the inclusion criteria

•Being a shift worker or having a very intensive night-time work schedule

•Remaining unstable despite the treatment or requiring regular adjustments of the treatment due to their clinical status

•Being a heavy drinker, consuming >280 g of alcohol per week in the case of men or >170 g for women

•Having congestive heart failure or moderate to severe chronic renal failure that is New York Heart Association (NYHA) stage ≥III or a glomerular filtration rate < 45 mL/min

•Patients having low blood pressure ≤ 110/60 mmHg

*Withdrawal criteria*:

•Undergoing changes in their treatment within the 5-month period of the trial

•Requiring admission to hospital during the clinical trial

### Recruitment process

Patients meeting the inclusion criteria will be identified using the electronic medical record systems, OSABIDE in Osakidetza and the SISAP in the Catalan Health Service. Considering the information in the medical record, each doctor will check the list of candidate patients, rejecting those that *a priori* meet any of the exclusion criteria, that is, cases in which inappropriate patients have been identified by the electronic selection process. After that, the trial monitor will review this first filtering by the doctors, to ensure that it has carried out been correctly, and patients will be randomly selected by a computer program in the PCRUB, until seven or eight patients have been included per doctor. A randomly-ordered back-up list of potential replacements will be prepared, to use in the event that any of these seven or eight initially selected patients decline to give informed consent or are excluded for not meeting the selection criteria. If the target population on any doctor’s list is too small, we will ask another doctor from the same health centre, who until that point has not been involved in the recruitment process, to grant us permission to identify patients within the target population on their list, following the aforementioned procedure for potential replacements. Once a patient is included in the study they will receive a letter, with a follow-up telephone call, inviting them to make an appointment with their general practitioner (GP). During this appointment, their doctor will explain the characteristics of the study and invite them to take part. If patients agree and sign the informed consent form, they will be included in the study population. At this point, their doctor will enter them in the electronic data capture (EDC) system, a code being automatically generated for that patient for the study. This code is formed by five digits: .

**A**: The first digit will correspond to the province where the patient is registered.

**A and B**: The first and second digits combined will indicate the patient’s health centre.

**A**, **B and C**: The code identifying doctors and nurses is based on the first three digits of each patient’s code, preceded by a D or N for doctors and nurses, respectively.

**D and E**: The last two digits of the code individually identify each of the patients.

Once the code has been generated, the doctor will enter data regarding patient registration, sociodemographic characteristics and clinical history, and make an appointment for the patient with a nurse.

### Randomisation

Randomisation will be performed in a 1:1 ratio using computer-generated random numbers provided by a central site, the Laboratorium Sanitatis. Specifically, when the medication pack number for each of the 258 patients participating in the study is associated with a single patient, this individual is randomly assigned to one of the two treatments: that is, having placebo at bedtime (administered between 20:00 and 22:00) and 100 mg of ASA in the mornings (administered between 08:00 and 10:00), on the one hand; or placebo in the mornings (administered between 08:00 and 10:00), and 100 mg of ASA at bedtime (administered between 20:00 and 22:00). After the washout period of 15 to 30 days, the patients start their medication for the second 2-month period of the study, and their treatment will have been swapped; that is, those who in the first period had the placebo at bedtime (between 20:00 and 22:00) and 100 mg of ASA in the mornings (administered between 08:00 and 10:00) will have the placebo in the mornings (administered between 08:00 and 10:00) and 100 mg of ASA at bedtime (between 20:00 and 22:00) in this second period, and vice versa.

Throughout the study, the patient’s doctor and nurse and the person carrying out the statistical analysis will be blind to when the patient is taking the active ingredient under study.

### Intervention

#### First period

Patients included in the study will be referred for a nursing appointment by their GP. In this appointment, the nurse will take several anthropometric measurements and measure blood pressure, after patients have rested for 5 min (initially, two readings, but if the difference is >5 mmHg another reading will be taken, and the final measurement will be the mean of the two or three readings obtained). The same day, urine and blood samples will be collected. Later, after explaining to patients what ABPM involves, they will be fitted with a portable blood pressure monitor. Patients will be asked to carry out their normal daily activities with few restrictions and provided with a notebook for them to write down the main events in their day, as well as the time they woke up, went to bed, et cetera.

Twenty-four hours after placing the ABPM device, patients will be seen again by a nurse in their health centre, for the monitoring system to be removed. At this point, the nurse will provide patients with their corresponding medication pack, which will be assigned with the randomisation code and recorded in the EDC system. This pack will consist of a box with two containers, one holding the medication to be taken in the morning and the other that for bedtime. Both containers will have enough pills to complete the entire 2 months of treatment. On completion of the first month, the patients will be seen again by a nurse, for the first follow-up visit. The participants will be reminded of the importance of taking the medication as instructed, that they must bring back the medication containers even if they are empty, and that they should record in their notebook any symptoms that they have at any point during the month that could be adverse effects and the day on which they had them. Finally, a new appointment will be made for the following month, by the nurse.

In the second follow-up visit, the nurse will check patient adherence to the treatment again, by counting the empty blisters and directly asking the patients about their daily intake of the drugs, whether they took the medication at the right time and whether there had been any changes with respect to their initial medication regimen. In the event of non-adherence and/or when new drugs had been introduced, the nurse will contact the research team, to decide whether the patient should continue or be withdrawn from the study. In addition, the nurse will be in charge of investigating whether there had been adverse effects and collect the empty blister packs. In the second follow-up visit, just before completion of the first period, the blood pressure monitor will be fitted on the patient for the second 24 h of ABPM. The following day, the nurse will remove the device, make an appointment for between 15 days and 1 month later, and provide the medication for this time, which corresponds to the washout period (see below). Then the first period of the trial will have been completed (Figure 1).

#### Washout period

Given the cross-over nature of this study, the first and second study periods are separated by a washout period of between 15 and 30 days. This must be of sufficient time for the effect of the drug taken during the first period to disappear and not interfere with the results of the effects of the drug taken in the second period. In this case, the same active ingredient is taken, but at different times of day. During the washout period, all the study patients will be asked to take ASA during the day as they did before the start of the trial. The duration of 15 to 30 days could seem to be excessively long as the half-life of ASA ranges from 2 to 20 h [16] and, indeed, even 1 week should be sufficient time for the drug to be cleared from the body and for any effects of bedtime administration to wear off. Nevertheless, for organisational reasons and so that ABPM measurements are further apart and interfere less with the patients’ daily life, we have opted for a variable washout period.

#### Second period

At the start of the second period, the nurse will set up the ABPM system for the patients for the third time. After removing the ABPM device, 24 h later, patients will be given the medication and instructions on how to take it over the following 2 months and an appointment with a nurse will be made for them the next month, as in the first period. In this second period, patients swap their treatment sequence: that is, those patients who had placebo at bedtime in the previous period (between 20:00 and 22:00) and 100 mg of ASA in the mornings (administered between 08:00 and 10:00) will take placebo in the morning (administered between 08:00 and 10:00) and 100 mg of ASA at bedtime (between 20:00 and 22:00) in this second period and, vice versa, those who in the first period had placebo in the morning (administered between 08:00 and 10:00) and 100 mg of ASA at bedtime (between 20:00 and 22:00) will now take placebo at bedtime (between 20:00 and 22:00) and 100 mg of ASA in the mornings (administered between 08:00 and 10:00). Some days before the end the second month of the second period, a fourth 24-h ABPM measurement will be taken, as will blood and urine samples. When the data from this second period have been transferred to the database and it has been confirmed that the blood test results are within normal ranges or that if there have been changes they are judged not to be clinically relevant by the research team, the trial will come to an end (Table 1).

**Table 1 T1:** Design of study

**Schedule of events (Day counted from the first visit, Day 0)**	***Screening: ******visit *****1 (Day −15)**	***Baseline*****, *****enrolment, ******randomization: ******visit 2 *****(Day 0)**	**Treatment: *****visit 3 *****day 30**	**Treatment *****visit 4 *****day 60**	**Treatment *****visit 5 *****day 90**	**Washout 1 month**	**Treatment *****visit 6 *****day 150**	**Treatment *****visit 7 *****day 180**	**Treatment *****visit 8 *****day 210**
**Study procedures**									
Informed consent form	X								
Medical history	X								
Physical examination including weight and height measurements		X							
Demographic data	X								
**Intervention**									
Control/Intervention group I (ASA in the morning and placebo in the evening in the first period)			X	X	X	Crossover	X	X	X
Intervention/Control group II (placebo in the morning and ASA in the evening in the first period)			X	X	X		X	X	X
**Blood chemistry**									
Haematology and biochemistry		X							X
**Efficacy measures**									
ABPM		X			X				X
**Safety assessment**			X	X	X		X	X	X

Each of the patients will be followed up over a period of 5 months.

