**Methods/Design:**

This is a prospective phase IV multicentre, randomised, triple-blind, placebo-controlled, cross-over clinical trial. We will include 258 individuals with hypertension treated with low-dose aspirin for secondary prevention. These patients will be randomly recruited, by approximately 40 primary care physicians collaborating in the study, mainly in the Guipúzcoa West, Bilbao and Barcelona areas. The 258 patients will be randomly allocated to treatments to create two comparable groups. In the first period, the intervention group will take aspirin at night and placebo in the morning, while the control group will take their aspirin in the morning and placebo in the evening for 2 months. After a washout period of 15 to 30 days, there will be a second 2-month period for which groups will swap treatments. Participants will undergo ambulatory blood pressure monitoring at baseline, at the end of first period and then again at the beginning and end of the second period. The main outcome measure is the change in mean blood pressure over 24 h, and as secondary outcomes we will also assess changes in systolic and diastolic blood pressure, during the day and night, and the relationship between them. Lastly, we will explore whether non-dipper patients convert into dippers with the intervention.

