### Analysis

First, an assessment will be made of the potential carry over effect of the treatment from the first period to baseline levels before the second period. The analysis will be carried out on an intention-to-treat basis, comparing the mean blood pressure at the end of the period of bedtime intake with that observed after the daytime intake, adjusting for the baseline blood pressure at the start of each period in all patients which at least have received one dose of treatment. Moreover, we will perform a per protocol analysis with only the patients have not change in their treatment within the 5-month period of the trial and have not been withdrawn. The effect attributable to bedtime intake will be estimated in terms of the difference in mean blood pressure between the two periods and the 95% confidence interval will be calculated using mixed-effect models analysis of covariance for repeated measures of blood pressure taken in each subject at the end of each of the periods. These models will include the patient as a random effect (intercept), to take into account the correlation between the two measurements in the same individual in each period. As well as adjusting for the baseline levels, we will adjust for potential confounding or modifying variables: changes in medication, period or sequence, age, sex, unhealthy habits as to be smoker or no smoker, risk factors as to be dipper or non-dipper comorbidity as diagnosis of dyslipemia, diabetes, stroke, peripheric arteriophaty or myocardial infarction and month of the year when the study is started. We will assess, by means of tests of interaction, the absence of a modifying effect of bedtime intake as a function of the period when patients took the ASA at this time.

A stratified analysis will be undertaken considering two groups, dippers and non-dippers, assuming that the prevalence of non-dippers in this population is 40%.

In the mixed-effect analysis, all the data available from each of the subjects included in the study will be considered, regardless of whether there is missing data. Values of missing data will not be imputed, except in the case of the baseline values for the second period, in which case they will be assigned the same value as the baseline measurements at the start of the study. It has been shown that this is more robust than other approaches to dealing with missing data.

All this analysis will be carried out using the SAS statistical package.

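### Table 1 contradicts the text: it schedules three ambulatory recordings instead of four, omits the one at the start of period 2, and ends at day 210 rather than 5 months

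*Protocol article*

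**What the plan says.** The text is consistent from section to section.

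- **Abstract, Methods/Design:** ABPM at baseline, at the end of period 1, and "then again at the beginning and end of the second period".
- **Study design:** "The results will be assessed by monitoring BP at baseline and 2, 3 and 5 months after the intervention".
- **Intervention, First period:** follow-up visits after one and two months, with medication supplied for two months. The second ABPM belongs to the second of these visits: "In the second follow-up visit, just before completion of the first period, the blood pressure monitor will be fitted on the patient".
- **Intervention, Second period:** "At the start of the second period, the nurse will set up the ABPM system for the patients for the third time". A fourth recording follows near the end of the second month.
- **Discussion:** four sets of ABPM measurements are presented as a deliberate choice.

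Table 1 differs. Its ABPM row is marked at visit 2 (day 0), visit 5 (day 90) and visit 8 (day 210). Treatment visits are listed at days 30, 60 and 90, then, after a 1-month washout, at days 150, 180 and 210. The line directly below the table reads "Each of the patients will be followed up over a period of 5 months".

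The Analysis section relies on the recording that the table leaves out. It begins by assessing the "potential carry over effect of the treatment from the first period to baseline levels before the second period", and it compares treatments "adjusting for the baseline blood pressure at the start of each period". Missing values are not imputed, with one exception. For missing period-2 baselines, "they will be assigned the same value as the baseline measurements at the start of the study".

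**The concern.** A schedule of events is the part of a protocol that tells staff what to do at each visit. The Abstract foresees about 40 physicians and the Setting section 20 centres. Anyone working from Table 1 would not record ABPM at the start of period 2 and would take the end-of-period recordings on the wrong days.

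The loss would be easy to miss. The analysis rule fills the gap with the study-start baseline, so the mixed model still runs. That value was measured before any study treatment, so it cannot differ between sequences because of what was taken in period 1, and the planned carry-over check would have nothing to detect. For patients with both periods, a covariate with the same value in both also cancels from the within-patient bedtime-minus-daytime difference, so the planned adjustment for each period's own baseline would do no work there.

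**Working it through.** **1. Duration.**

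Text: period 1 (60 days) + washout (15 to 30 days) + period 2 (60 days).

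- Shortest: 60 + 15 + 60 = 135 days.
- Longest: 60 + 30 + 60 = 150 days. This reproduces the stated 5 months.

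Table 1: the last visit is at day 210, counted from day 0, or about 7 months. The excess is 210 − 150 = 60 days to 210 − 135 = 75 days.

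**2. Recordings.**

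| Time point | Text | Table 1 |
|---|---|---|
| Baseline | day 0 | day 0 |
| End of period 1 | about day 60 | day 90 |
| Start of period 2 | about day 75–90 | not marked |
| End of period 2 | about day 135–150 | day 210 |
| Total | 4 | 3 |

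The ABPM row has ten cells (a label and nine columns), the same number as the header. A shift in text extraction is therefore an unlikely explanation. The day labels show the duration conflict without relying on any mark.

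**3. Does another reading of the table rescue it?** The table prints no start day for period 2, so two readings are possible.

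- *Periods on days 0–90 and about 120–210* (90 + 30 = 120; 210 − 120 = 90). Each period lasts three months instead of two, and there is no visit column at the start of period 2.
- *Periods on days 30–90 and 150–210.* Each period lasts 60 days and visit 6 would start period 2, but its ABPM cell is empty.

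On neither reading is the start-of-period-2 ABPM scheduled.

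**4. What the carry-over check would lose.** The article does not name the test. I assume a two-sided 5% t-test between sequences on the period-2 baseline, with SD 8 mmHg (Sample size section). I take a carry-over of 2.5 mmHg, equal to the full treatment difference used in the sample size.

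- 129 per sequence: SE = 8 × √(2/129) = 0.996; 2.5/0.996 = 2.51; power 0.706.
- After the planned losses, 129 × 0.95 × 0.85 = 104 per sequence: SE = 8 × √(2/104) = 1.109; 2.5/1.109 = 2.25; power 0.611.

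A simulation (4000 runs, 129 per sequence, intra-subject correlation 0.5) compared measured baselines with study-start values substituted for every patient.

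| True carry-over (mmHg) | Rejection rate, measured | Rejection rate, substituted |
|---|---|---|
| 0 | 0.047 | 0.054 |
| 2.5 | 0.707 | 0.056 |
| 5 | 0.999 | 0.053 |

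With substituted values the test rejects at about its 5% false-positive rate whatever the carry-over.

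**5. The covariate.** In one simulated complete data set, a random-intercept model gave a treatment estimate of −1.704 (SE 0.528) both with no baseline and with the same baseline in both periods. This illustrates the cancellation. It does not measure what is lost relative to measured period-2 baselines.

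**The case against.** The conflict itself is hard to dispute. The case on the other side concerns how much it matters.

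- **Sites may never see this table.** It stands in a journal article. At submission 104 patients had been recruited under an authorised protocol that is not shown. The text also makes the table hard to follow: medication is supplied for two months, and period-2 medication is handed out only after the third ABPM has been removed. This stands. Harm is possible but not shown.
- **Another test of carry-over remains.** The Analysis section plans an interaction test of the bedtime effect by period. In a two-sequence, two-period design that is the sequence contrast, which needs no period-2 baseline. This is correct, but the test is weaker. For a patient's sum over both periods, SD = √(2 × 64 × 1.5) = 13.86. With 129 per sequence, SE = 13.86 × √(2/129) = 1.73, giving about 30% power for 2.5 mmHg against 71% for the baseline check. Some information on carry-over survives, but the interaction test does not replace that check.
- **A carry-over of 2.5 mmHg is extreme.** It assumes that the whole expected effect persists through the washout, while the article expects it to fade within about a week. At half that size (1.25 mmHg), even measured baselines give only about 24% power with 129 per sequence and 20% with 104. This stands, so the 71% figure is an upper case.
- **No harm to the primary estimate is quantified.** True. No bias or loss of precision in the bedtime-minus-daytime difference has been shown.
- **The visit counts are not clearly different.** Table 1 lists six treatment visits and the text four follow-up visits. On the second reading in step 3, visits 3 and 6 would be start visits, and the text also has a start contact in each period, so the count is six against six. I place no weight on this count.

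**Conclusion.** The concern holds. Table 1 contradicts consistent text on three points: three ABPMs against four, no ABPM at the start of period 2, and an end at day 210 against day 135–150. These follow from counting and addition and need no assumption.

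The statistical consequence is conditional. It arises only where the table is followed, and it falls on the period-2 baseline. The figures of 71% (or 61%) against 5% describe the limiting case in which no patient has that measurement. They rest on the assumed t-test, SD 8 mmHg and a carry-over as large as the whole expected effect. The sample size does not depend on this point. It should be corrected, but it does not undermine the design described in the text.

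**What to change.** Bring Table 1 into line with the text:

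- period 1 visits at days 30 and 60;
- a washout of 15 to 30 days in place of 1 month;
- a visit column for the start of period 2 at about day 75–90;
- period 2 visits 30 and 60 days after that, ending at about day 135–150;
- ABPM marked four times: day 0, about day 60, about day 75–90 and about day 135–150.

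Send the corrected table to the sites. The cost is one table and a note. It adds no patients, and no procedures beyond those the text already plans. With 104 of 258 patients recruited at submission, the correction would come in time for the other 154 and for any recruited patient who has not yet reached period 2.
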